**Figure 2 f2:**
[figure not shown]
Recruitment centers and specific altitude.

**Table 1 T1:** Items and procedures of the study at baseline and each follow-up.

	Baseline	1 year ± 30 days	2 years ± 30 days	3 years ± 30 days	4 years ± 30 days	5 years ± 30 days
Informed consent	X	–	–	–	–	–
Questionnaire survey	X	X	X	X	X	X
Muscle strength assessment (HGS)	X	X	X	X	X	X
Short physical performance battery (SPPB)	X	X	X	X	X	X
QCT scan	X	X	X	X	X	X
DXA scan	X^*^	X^*^	X^*^	X^*^	–	X^*^
Ultrasonic	X^*^	X^*^	X^*^	X^*^	–	X^*^
Blood collection	X^*^	X^*^	X^*^	X^*^	X^*^	X^*^

X, an item that will be collected.

X^*^, item that will be selectively carried out in viable centers.

-, item that will not be collected.

Ethical approval for the cohort study is obtained from the ethics committee of each study center [Main study center-The First People’s Hospital of Yunnan Province No. KHLL2021-KY056]. The study is conducted by ethical principles according to the Declaration of Helsinki. Radiation safety and protection measures are strictly implemented throughout the study. Informed consent is obtained from each participant at the nearest participating imaging center.

### The estimation of sample size

The sample size necessary for this study is set at 4000. The overall prevalence of osteoporosis at the femoral neck in adults aged above 50 years was reported to be 16%, or even up to 30% in postmenopausal women (29, 42). The overall prevalence of sarcopenia was reported to range from 5.5% to 25.7% (30). Thus, the number of 4000 is set to get the estimated overall prevalence of osteoporosis to be within 5% of the prevalence in the real world and considering the attrition rate of about 10%. This number is also needed to detect a significant difference (at least 5%) in prevalence proportions between the highest level of altitude and the lowest one. This number is also needed to detect significant results from the prospective cohort (survival analysis) with a two-tailed level of significance of 5% and statistical power of 80% when a risk factor for osteoporotic fracture is assumed to exist in 20% of participants at baseline and to increase a background fracture risk of 6% by 50% during the 5-year follow-up period. The SPSS 26.0 software (IBM, Armonk, NY, United States) will be chosen. The level of significance desired for this study is α=0.05, with a power level of β=0.2.

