The musculoskeletal system operates as a finely coordinated unit, interconnected not only by mechanical aspects but also by humoral factors. Muscle seems to possess the “upper hand” in its relationship with bone (38). Muscle loading induces a range of biomechanical signals necessary for bone growth and remodeling. Also, osteoporosis or fractures will lead to muscle atrophy and muscle mass reduction (38). Indeed, several muscles and bone-derived hormones (e.g., leptin, insulin, GH/IGF-1, myostatin, FGF2, and sexual steroids) are under active investigation to better explain the complex cross-talk and discrete hormonal influences between muscle and bone (38). Therefore, simultaneous assessment of bone and muscle may help gain a more complete picture of disease prevention and treatment in a certain area.

High altitude is generally defined as an altitude higher than 1500m above sea level, which is further classified into three grades: high altitude (1500-3500m); ultra-high altitude (3500-5500m); and very high altitude (>5500 meters) (39). The main environmental stressor associated with high altitude is decreasing atmospheric oxygen pressure. Other environmental stressors include low temperatures, humidity, and increased ultraviolet radiation (40). The impact of altitude on the musculoskeletal system is diverse and contingent upon the altitude in question. Existing studies are limited by their designs for comparison between two altitudes (26, 41). As a result, studies at different altitudes cannot be directly compared. Multi-altitude control studies can comprehensively depict the changes in the musculoskeletal system at different altitudes.

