### Recruitment strategy

The enrolment of potential subjects is assessed by investigators at each clinical center according to the inclusion and exclusion criteria. Each subject will sign an informed consent form before officially entering the study. The subjects of the SOY study are enrolled in 12 centers at different altitudes (**Figure 2**). The inclusion criteria are that participants should be aged over 50 years old and living at the research site for more than 10 years. Exclusion criteria were as follows: a. Inability to stand or walk independently; b. Deformity of the lumbar spine and hip joint; c. Tumors treated with radiotherapy or chemotherapy; d. Patients with metallic implants *in vivo*; e. Other serious or life-threatening diseases (e.g. severe stroke). Recruitment will start in August 2022 except for the main study center the First People’s Hospital of Yunnan Province in which recruitment started in April 2021. Baseline visits and follow-up details are shown in **Table 1**.

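### The stated 5-point detectable difference between highest and lowest altitude holds only if centres are pooled into a few bands with little centre effect; with 12 single-centre levels, power for osteoporosis is about 28–47%

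*Protocol article*

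**What the plan says.** The sample size section of the protocol article opens with "The sample size necessary for this study is set at 4000" and gives three justifications for the number: precision of the overall prevalence, an altitude contrast, and a fracture analysis. For altitude, it says the number is needed to "detect a significant difference (at least 5%) in prevalence proportions between the highest level of altitude and the lowest one".

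The section closes with "The level of significance desired for this study is α=0.05, with a power level of β=0.2", which amounts to 80% power. The fracture justification specifies its test "with a two-tailed level of significance of 5% and statistical power of 80" per cent; sidedness is not repeated for the altitude contrast.

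The background rates in the same section are osteoporosis, which "was reported to be 16%, or even up to 30% in postmenopausal women", and sarcopenia: "The overall prevalence of sarcopenia was reported to range from 5.5% to 25.7" per cent.

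On the design, Recruitment strategy says: "The subjects of the SOY study are enrolled in 12 centers at different altitudes". The Introduction gives the altitude range as 50 to 3500 m and offers one grading of altitude: "High altitude is generally defined as an altitude higher than 1500m above sea level, which is further classified into three grades". No readable text says how many altitude levels the contrast has, how many participants each holds, or which baseline prevalence it assumes.

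**The concern.** A highest-versus-lowest comparison draws its information from two groups only. Participants at intermediate altitudes add nothing to it, so a total of 4000 says little until it is known how many levels share that total. The article cites the full 4000 in support of the contrast and attaches no condition.

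Comparing prevalence across altitudes is the first primary aim, and this sentence is the only power statement that addresses it. If the contrast has much less than 80% power, a non-significant result could be reported as evidence against a 5-point difference that the study was unlikely to detect.

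**Working it through.** **Inputs.** From the sample size section: total 4000, alpha 0.05, beta 0.2, osteoporosis 16% and 30%, sarcopenia 5.5% and 25.7%, attrition 10%. From Recruitment strategy: 12 centres. Assumptions, since the article does not state them: a two-sided test, 5% read as percentage points, and equal level sizes. Attrition is not applied to the contrast, because prevalence is compared at baseline.

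**Step 1: where 4000 comes from.** The fracture inputs are 6% versus 9% risk with 20% exposed. A pooled-variance two-proportion formula at two-sided 5% and 80% power gives 2879 unexposed + 720 exposed = 3599, and 3599 / 0.90 = 3999. The article does not name its formula, and event-based survival formulas give a larger total, but this match is close. The precision goal (within 5 points) needs only 207 at 16% and 323 at 30%. So 4000 is reproduced by the fracture calculation. The altitude contrast needs its own check.

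**Step 2: formulas.** With d = |p1 − p2| and p̄ = (p1 + p2)/2:

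- n per level = [1.96·√(2p̄(1−p̄)) + 0.842·√(p1(1−p1) + p2(1−p2))]² / d²
- power = Φ{ [d·√n − 1.96·√(2p̄(1−p̄))] / √(p1(1−p1) + p2(1−p2)) }

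**Step 3: each centre as a level.** 4000 / 12 ≈ 333 per level.

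- 16 v 21%: (0.05·√333 − 1.96·0.549) / 0.548 = (0.912 − 1.076) / 0.548 = −0.30, so power is 38%.
- 30 v 35%: (0.912 − 1.96·0.662) / 0.661 = −0.58, so power is 28%.
- Falls: 16 v 11% gives 47%; 30 v 25% gives 30%.
- Sarcopenia: 5.5 v 10.5% gives 66%; 25.7 v 30.7% gives 30%. A fall from 5.5 to 0.5% gives 97%.
- The n per level for 80% power is 946 (16 v 21%) or 1377 (30 v 35%). Over 12 equal levels that is 12 × 946 = 11,352 or 12 × 1377 = 16,524.
- Solving the power formula for d at 333 per level gives a detectable rise of about 8.7 points from 16% and 10.3 points from 30%.

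**Step 4: centres pooled into equal bands, no centre effect.** Power for a 5-point rise in osteoporosis:

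| Levels | n per level | 16 v 21% | 30 v 35% |
|---|---|---|---|
| 2 | 2000 | 98% | 92% |
| 3 | 1333 | 91% | 79% |
| 4 | 1000 | 82% | 67% |
| 5 | 800 | 73% | 57% |
| 6 | 667 | 65% | 50% |
| 12 | 333 | 38% | 28% |

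At 16% the claim is met with up to four levels (4 × 946 = 3784). At 30% it is met for a rise with two levels (2 × 1377 = 2754) and just missed with three (3 × 1377 = 4131). For a fall from 30%, three levels give 82%.

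**Step 5: centre effect in the most favourable case.** Altitude varies only between centres, so variation between centres enters the contrast directly. The article gives no intraclass correlation (ICC); the values below are assumptions to show sensitivity. The design effect is 1 + 332·ICC, and the effective n per band is 2000 divided by it.

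| Assumed ICC | Design effect | Effective n per band | 16 v 21% | 30 v 35% |
|---|---|---|---|---|
| 0 | 1.00 | 2000 | 98% | 92% |
| 0.001 | 1.33 | 1502 | 94% | 83% |
| 0.005 | 2.66 | 752 | 70% | 54% |
| 0.01 | 4.32 | 463 | 50% | 37% |

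**The case against.** The strongest reply is that a level need not be a centre. The sentence compares levels of altitude, no readable text equates the two, and the figure listing centres and altitudes is not available here. The Introduction's grading, applied to 50–3500 m, gives essentially two bands, below and above 1500 m, and with two equal bands the claim is met comfortably before any centre effect. This stands. A reader might infer from the 12-centre figures that the 5-point claim is simply false; the documents do not support that, because they state neither single-centre levels nor equal centre sizes.

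The reply goes only so far. The Introduction criticises earlier work for comparing just two altitudes, and the Discussion presents this study as the first multicentre cohort with several altitude levels. Two bands would rescue the arithmetic but sit poorly with that rationale.

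Three further points are fair. The 30% figure is an upper value for postmenopausal women, so 16% is the better guide for the whole sample; on 16% alone the 12-level range is 38–47%. The ICC values are assumed and none should be presented as the study's own. And an article may leave details of grouping to a fuller document. The finding is therefore not that a detail is missing, but that a definite power claim is made without the condition on which it depends.

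**Conclusion.** The point holds in conditional form. The statement that 4000 detects a 5-point difference between extreme altitudes at 80% power is true for some groupings of the centres and not for others, and the article does not say which applies. With 12 equal single-centre levels, osteoporosis power is 28–47% across both prevalences and both directions. With pooled bands and no centre effect, a 5-point rise is detectable at both prevalences only with two bands, and at 16% alone with up to four. At an assumed ICC of 0.005, even two bands fall below 80%.

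These results rest on equal level sizes, a two-sided test and an absolute 5 points. A reader might also infer that 4000 is too small for the study; that does not follow, since the total matches the fracture inputs and is unaffected by this point. Low-prevalence sarcopenia also fares better than osteoporosis.

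**What to change.** In the sample size section, state the altitude levels used for this contrast, the number of participants expected in each, and the baseline prevalence assumed. Replace 5% with the difference detectable at 80% power for those levels: about 9 to 10 points for a rise in osteoporosis if each centre is a level. Say either that this is before any centre effect, or give it over a stated range of assumed ICCs.

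Optionally, report the altitude trend across all centres from the regression already planned under Statistical analysis. It uses every participant rather than the two extremes, though it too is exposed to variation between centres.

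The cost is text only, with no change to 4000. The downside is that the stated detectable difference may become less favourable.

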### Baseline visit

The demographic information, anthropomorphic measures, questionnaires, muscle strength assessment, short physical performance battery (SPPB), collection of blood samples, and imaging assessments (QCT and/or DXA, US) are scheduled to be conducted on each participant.

Detailed demographic measures include age, biological age calculated based on somatic variables (43), gender, ethnicity, residence, education, occupational status, daily physical questionnaire (IPAQ), eating habits (e.g. tea intake, vegans, red meat/white meat intake/both), fall risk screening, fracture history (time/frequency/fracture site), alcohol intake, smoking history, medical history (calcium/vitamin D/hormone), menopausal age, fall history (time, frequency, location), disease history (rheumatoid arthritis/secondary osteoporosis).

Anthropomorphic measures consist of height, weight, waist, and maximum calf circumference. The SARC-F questionnaire will be used to predict potential persons with sarcopenia at risk for poor functional outcomes (described below **Table 2**).

**Table 2 T2:** SARC-F questionnaire.

Component	Question	Score
Strength	How much difficulty do you have in lifting and carrying 10 pounds?	one = 0 Some = 1 A lot or unable = 2
Assistance in walking	How much difficulty do you have walking across a room?	None = 0 Some = 1 A lot, use aids, or unable = 2
Rise from a chair	How much difficulty do you have transferring from a chair or bed?	None = 0 Some = 1 A lot or unable without help = 2
Climb stairs	How much difficulty do you have climbing a flight of 10 stairs?	None = 0 Some = 1 A lot or unable = 2
Falls	How many times have you fallen in the past year?	None = 0 1-3 falls = 1 4 or more falls = 2

Muscle strength assessment with HGS. HGS of the dominant hand will be measured using a Jamar dynamometer (Jamar, Los Angeles, CA), two attempts with a 30-second interval between them were recorded in kilograms, and the maximum value will be chosen for further analysis.

A short physical performance battery (SPPB) includes a 4m gait speed (GS), a five-times repeated chair sit-to-stand (STS) and a balance test (semi-tandem, full-tandem, and single-leg stand time) will be recorded.

Blood sample collection is mainly for laboratory examination, such as hepatic and renal function, 25(OH)D, BGP, PTH, Calcium, biochemical markers of bone turnover, biochemical markers of bone metabolism, leptin, insulin, GH/IGF-1, myostatin, FGF2, and sex steroids.

Imaging assessments include abdomen quantitative computed tomography (QCT), dual-energy X-ray absorptiometry (DXA), and appendicular limb ultrasound. Evaluation indicators include muscle density, muscle size, intermuscular fat size, BMD (measured by QCT and/or DXA), and whole-body composition analysis. The trunk muscle, gluteus muscle, and appendicular limb muscle are the object muscles being evaluated. The BMD values (mg/cm^3^) of the L1 and L2 vertebral bodies are measured according to the QCT protocol (44) (**Figure 3**). The spinal vBMD was represented by the average vBMD value of L1–L2. In each subject, abdominal CT scans with a Mindways calibrated QCT acquisition phantom (Mindways Software Inc, Austin, TX, USA). For cross-calibration, a single European Spine Phantom (ESP-122) will be scanned at all centers before scanning the subjects.

**Figure 3 f3:**
[figure not shown]
Dual-energy X-ray absorptiometry (DXA) and computed tomography (CT) assessments. **(A)**: the whole body DXA scan for body composition analysis, mainly for the evaluation of muscle and fat mass. **(B)**: Areal BMD was calculated by the DXA scan of the lumbar spine and left hip. **(C)**~**(F)**: Muscle assessments with QCT including muscle density, muscle area, and intermuscular fat area. **(C)**: Measurement of trunk muscle at mid-L2 level; **(D)**: Measurement of cross-sectional area and mean computed tomography values of the gluteus maximus muscle at the level of the greater trochanter of the femur; **(E)**: Measurement of the gluteus medius and minimus muscle at the third sacral level; **(F)**: Measurement of the middle thigh muscle level. The muscle region is represented by the area highlighted in red. The area of intramuscular fat infiltration is obtained by subtracting the area of red ROI from the area of green ROI with the threshold segmentation method.

Notably, QCT is a required item for all research centers.

### Follow-up visit

A 5-year follow-up will be conducted to evaluate the changes in muscle size, density, and fat infiltration in different muscles, the decrease of BMD, muscle function impairment, and osteoporotic fracture incidence. Details of the assessments of the follow-up visits are shown in **Table 1**.

### The diagnosis criteria of osteoporosis

The diagnostic criteria of osteoporosis for QCT, recommended by the International Society for Clinical Densitometry in 2007 (45) and the American College of Radiology in 2008 (46), are used to classify the subjects as normal if average vBMD >120 mg/cm^3^, osteopenia if vBMD between 120 and 80 mg/cm^3^, and osteoporosis if vBMD <80 mg/cm^3^.

### The diagnosis criteria of sarcopenia

According to the 2019 consensus update on sarcopenia diagnosis and treatment of the Asian working group for sarcopenia (AWGS 2019), the new diagnosis of sarcopenia was low muscle mass accompanied by low muscle strength or low physical performance. AWGS 2019 also defines persons with low muscle mass, low muscle strength, and low physical performance as having “severe sarcopenia” (30).

The specified cutoffs for each diagnostic component were as followed: low muscle strength was defined as handgrip strength < 28 kg for men and <18 kg for women; criteria for low physical performance were 6-m walk<1.0 m/s, short physical performance battery(SPPB) score ≤ 9, or 5-time chair stand test ≤ 12 seconds. Muscle mass assessment was retained the original cutoffs for height-adjusted: dual-energy X-ray absorptiometry<7.0 kg/m^2^ in men and <5.4 kg/m^2^ in women; and bioimpedance<7.0 kg/m^2^ in men and <5.7 kg/m^2^ in women.

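### The chair-stand cut-off for low physical performance points the wrong way: as printed, fast risers count as impaired, which distorts the sarcopenia classification behind the first primary aim.

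*Protocol article*

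**What the plan says.** The section on the diagnosis criteria of sarcopenia adopts the AWGS 2019 consensus. Sarcopenia is "low muscle mass accompanied by low muscle strength or low physical performance", and the section describes "persons with low muscle mass, low muscle strength, and low physical performance as having" the severe form.

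The cut-offs for strength and performance stand in one sentence:

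- Strength: "low muscle strength was defined as handgrip strength < 28 kg for men and <18 kg for women".
- Performance, first two limbs: "criteria for low physical performance were 6-m walk<1.0 m/s, short physical performance battery(SPPB) score ≤ 9".
- Performance, third limb: "or 5-time chair stand test ≤ 12 seconds".

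The Baseline visit section says which function tests are done. Besides handgrip there is the SPPB, which "includes a 4m gait speed (GS), a five-times repeated chair sit-to-stand (STS) and a balance test". Table 1 lists handgrip and SPPB as the only function tests at every visit. A 6-m walk appears only in the diagnostic criterion.

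The Introduction makes baseline sarcopenia prevalence at different altitudes part of the first primary aim, and the Statistical analysis section repeats it as a planned cross-sectional comparison.

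**The concern.** The chair stand is a time to complete a fixed five rises, so a long time is poor performance. The printed limb attaches the label of low performance to times of 12 s or less. It is the only cut-off in its sentence that picks out the better performers.

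The five-times chair stand is also one component of the SPPB, and a low SPPB total counts as impairment. Assuming that a slower chair stand lowers the SPPB score (the article does not print the item scoring), the same measurement enters the rule in two opposite directions.

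Because the limbs are alternatives, one inverted limb is enough to decide the component: anyone who finishes within 12 s has low performance whatever the other tests show. At stake are the sarcopenia and severe-sarcopenia labels and the comparison of their prevalence between altitudes. If chair-stand speed itself varies with altitude, the inverted limb pushes that comparison in the wrong direction and does not merely add noise.

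**Working it through.** **Step 1: direction of each cut-off in the sentence.**

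| Criterion | Counts as low | Who is flagged |
|---|---|---|
| Handgrip | < 28 kg men, < 18 kg women | weaker |
| Walk | < 1.0 m/s | slower |
| SPPB | ≤ 9 | lower score |
| Chair stand | ≤ 12 s | **faster** |

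**Step 2: effect on the class of a person with low muscle mass.** Let S, W, B and C stand for low strength, low walk, low SPPB and chair stand in 12 s or less.

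- Performance as printed: P = W or B or C.
- Performance with the sign turned: P′ = W or B or not-C.
- Class: severe if S and P; sarcopenia if exactly one of S and P holds; none otherwise.

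There are 2 × 2 × 2 × 2 = 16 patterns. If W or B holds (3 of the 4 walk/SPPB combinations, so 3 × 4 = 12 patterns), performance is low under either sign and nothing changes. In the other 1 × 4 = 4 patterns, with adequate walk and SPPB above 9, the chair stand alone decides, and all four change:

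| Strength | Chair stand | As printed | Sign turned |
|---|---|---|---|
| normal | ≤ 12 s | sarcopenia | none |
| normal | > 12 s | none | sarcopenia |
| low | ≤ 12 s | severe | sarcopenia, not severe |
| low | > 12 s | sarcopenia, not severe | severe |

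The 16 patterns are not equally common, so 4 of 16 is not a share of participants.

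**Step 3: share meeting the chair-stand limb (assumed inputs).** The article gives no chair-stand distribution. Take a normal distribution with mean 10 to 12 s and SD 3 to 4 s. Then P(T ≤ 12) = Φ((12 − mean)/SD):

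- mean 10, SD 3: Φ(0.67) = 0.75
- mean 11, SD 3.5: Φ(0.29) = 0.61
- mean 12, SD 4: Φ(0) = 0.50

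The printed limb would flag 50–75% of participants and the turned limb the complementary 25–50%. This describes one limb only.

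**Step 4: share with low performance over all three limbs (assumed inputs).** Let q be the share finishing within 12 s (0.4 to 0.8), c the share of slower risers caught by walk or SPPB (0.3 or 0.7), and f = 0.1 the share of faster risers so caught.

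- As printed: q + (1 − q)c
- Sign turned: (1 − q) + qf
- Status changes: q(1 − f) + (1 − q)(1 − c)

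| q | c | As printed | Sign turned | Status changes |
|---|---|---|---|---|
| 0.4 | 0.3 | 58% | 64% | 78% |
| 0.4 | 0.7 | 82% | 64% | 54% |
| 0.6 | 0.3 | 72% | 46% | 82% |
| 0.6 | 0.7 | 88% | 46% | 66% |
| 0.8 | 0.3 | 86% | 28% | 86% |
| 0.8 | 0.7 | 94% | 28% | 78% |

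The table also shows how a contrast can turn over. Suppose c = 0.3 and fast risers make up 80% at one altitude and 40% at another. With the sign turned, low performance goes from 28% to 64%; as printed it goes from 86% to 58%. The site with slower risers then looks better. These are shares of the performance component, not of sarcopenia, which also needs low muscle mass.

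**The case against.** The best defence is that the section recites a published consensus, and one sign at odds with its own sentence looks like a transcription slip. Misclassification follows only if the derivation program copies the sign, and the article does not show that it does. This stands as a limit on what can be predicted, but it does not rescue the printed rule: nothing elsewhere in the article corrects it, and it is the definition that centres and programmers have to work from.

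The reach is also limited. Sarcopenia requires low muscle mass, which the criteria define only by DXA or bioimpedance. Table 1 makes DXA optional by centre, and no bioimpedance measurement is listed. Slow risers are partly protected, because a low SPPB can still catch them. All of this stands and narrows the effect without removing it.

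Two stronger readings are tempting and not supported:

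- *The QCT cut-offs for sarcopenia inherit the error.* The Statistical analysis section sets them at the 20th percentile of each variable's distribution, not by calibration against the AWGS diagnosis, so the chair-stand sign does not enter.
- *The walk limb cannot be computed.* The criterion, "criteria for low physical performance were 6-m walk<1.0 m/s", is a speed, and a 4-m gait speed in the same unit can be derived. The course lengths differ and the article does not say how they are reconciled. That is a gap to close, not an impossibility. The listed bioimpedance cut-offs, likewise without a matching measurement, suggest that the section sets out the consensus's alternatives rather than only the tests used.

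**Conclusion.** The point holds for the chair-stand limb. As printed it is wrong in direction, which can be seen from the article alone. Followed literally, it changes the class of every participant with low muscle mass whose walk is adequate and whose SPPB is above 9: with normal strength it creates false cases among fast risers and misses slow ones, and with low strength it swaps severe and non-severe. This feeds directly into the prevalence comparison of the first primary aim.

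The size of the effect on prevalence, or on the altitude contrast, cannot be computed from the article. A reader might take 50–75% as the share of participants misclassified or wrongly called sarcopenic. It is neither: it is the share meeting one limb, under an assumed normal distribution. The 54–86% changing status on the performance component rests on assumed inputs too. The mismatch between the 6-m and 4-m walk is secondary.

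**What to change.** 1. Turn the inequality so that slow chair-stand times count as low performance. Take the handling of exactly 12 s from the cited AWGS 2019 consensus, which is not at hand here.
2. Check that the derivation program for low performance, sarcopenia and severe sarcopenia uses the corrected direction, and re-derive any classification already made.
3. As a minor reconciliation, either drop the walk limb and classify on SPPB and chair stand, or state that the speed threshold is applied to the 4-m test.

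The cost is a one-line correction to the criteria, one sentence on the walk, and a check of the code. The chair-stand time is already part of the SPPB at each visit, so no new data are needed.
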